### Data collection methods

Pharmacists will collect data during their intervention at three time points during the study: at recruitment time, six months later and twelve months after the first encounter. A validated tool will be used for identifying and documenting DRPs, the PharmDISC tool [15] (PharmDISC tool will be used only including the 15 DRPs related to patients’ behavior out of the 24 total DRP). In addition, a questionnaire including seven questions to evaluate patients’ medication knowledge will be used. Pharmacist may choose to complete all documents (medication plan and patients’ medication knowledge questionnaire which are merged in a single document, and, if any DRP is detected, the PharmDISC tool) in paper or electronic version during each consultation with the patient.

Participant pharmacists must complete a sociodemographic questionnaire about CP characteristics and his/her individual characteristics during the educational training. This questionnaire on paper will be collected at the end of the study. In addition, pharmacists should complete an electronic anonymous satisfaction questionnaire after each pharmacist-patient consultation. The time taken per patient to deliver the intervention (differentiated between pharmacist and pharmacy technician time) will be recorded. After coding data, champion pharmacists will send a copy of the data collected to the research team within one month after each consultation and/or contacting the GP when necessary. The research team will evaluate the documents to ensure quality of service provision and fidelity to the study protocol. Pharmacists will receive a remuneration of CHF 100 per pharmacist-patient consultation (which cannot be financed by the basic health insurance) and an additional amount of CHF 10 for the additional time spent on documentation of consultations and interventions for research purposes according to the guidelines given in the educational training. The amount of CHF 100 was calculated by the time expected for each professional involved in the service: approximately 45 minutes for pharmacists (CHF 87 per hour) and approximately 45 minutes for pharmacy technicians (CHF 53 per hour).

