Number of pharmaceutical interventions (quantitative)	Number of interventions carried out by the pharmacist to correct DRPs and/or prevent their consequence. Total number of interventions and mean per pharmacist, per patient, per number of medications and number of DRPs identified will be calculated.	Pharmacists will complete the PharmDISC tool before and during the consultation.
Pharmaceutical interventions classification (qualitative)	Classification of interventions will be made using PharmDISC tool: • Substitution • Dose adjustment • Adjustment of the delivery amount (package size, quantity of packages, etc.) • Optimization of administration / Change of administration way • Therapy stopped/no delivery • Therapy started • Counselling of patient • Application/use instruction (training) • Delivery of an adherence aid inclusive counselling • Clarification in the case notes (history) • Information to the GP • Therapy monitoring • -Other	Pharmacists will complete the PharmDISC tool before and during the consultation.
Pharmaceutical interventions acceptance (quantitative)	Pharmaceutical interventions acceptance by the patient or the GP (when proposed to the GP, it will be considered as accepted unless the GP states otherwise). Number and proportion of intervention accepted versus proposed according to the number of medications and the number of DRPs.	Pharmacists will complete the PharmDISC tool during the second and third consultation.
**Secondary outcomes**	**Definition and assessment**	**Time point**
Number of removed medications (quantitative)	Expired or in bad condition or unused medications will be identified after reviewing the medication brought by the patient to the pharmacy: total number, mean per patient and percentage in relation to the total medication brought by the patient will be documented.	Pharmacists will complete the medication plan during the consultation with patients.
Number of removed medications discharged (quantitative)	Number of medications proposed to be removed and accepted by the patient after pharmacist-patient consultation: total number, mean per patient and percentage in relation to the total expired medication identified will be documented.	Pharmacists will complete the medication plan during the consultation.

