### Statistical methods and analysis

Continuous variables will be summarized using mean and standard deviation, or median and percentiles depending on the distribution of the variable. To assess normality, the Kolmogorov Smirnov test will be used. Categorical variables will be reported by frequency and proportion. For the comparison of continuous variables, the T Student’s test or the ANOVA test will be carried out if there is a normal distribution, and Kruskal-Wallis otherwise. The comparison of the categorical variables will be carried out using the χ2 test, the Fisher’s exact test or Yate’s chi-squared test if necessary.

For each patient, differences between consultations (second and first consultations, third and first consultations) will be compared for dependent variables (number of DRPs and medication expired, patient knowledge score, pharmaceutical interventions and medication removed, proportion of pharmaceutical interventions acceptance). A linear regression model will be performed accounting for the cluster effect. A cluster effect is expected by the way pharmacists interact with their team and the surrounding GPs, this could influence the number and type of DRPs detected and interventions made. A sub analysis will be carried out to evaluate the effect of patients undertaking or not a pre-selection of their medication before attending the pharmacy. Firstly, variables will be considered significant (p-value<0.2) in a bivariate model to be included in a multivariate model. Secondly, the variables considered significant at a value of p<0.1 in the multivariate model will be included in the final model. The level of significance will be set at p<0.05; the software STATA 17® will be used. An analysis with completed cases will be made (patients with data for the three consultations). In addition, an analysis with the whole sample will be made where, for the management of missing data, initial value will be considered as not been modified (baseline observation carried forward-BOCF) [28]. In case of a sufficient number of patients who are 65 years old or over are randomly included in the study, a sub analysis will be carried out to target the intervention to a specific group of patients with higher risk for DRPs [29, 30].

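### Acceptance is planned as a per-patient difference in proportions, which has no value when a consultation produced no intervention; the two planned analyses then handle those patients in different and unsuitable ways

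*Protocol article*

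**What the plan says.** Under Statistical methods and analysis the protocol fixes the unit and the contrast: "For each patient, differences between consultations (second and first consultations, third and first consultations) will be compared for dependent variables". The bracketed list of variables ends with "proportion of pharmaceutical interventions acceptance", and a linear regression allowing for clustering follows.

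Table 1 places acceptance among the primary outcomes and defines it as "Number and proportion of intervention accepted versus proposed according to the number of medications and the number of DRPs". The row on the number of interventions ties them to DRPs: "Number of interventions carried out by the pharmacist to correct DRPs and/or prevent their consequence". Data collection methods makes the recording form conditional: it is filled in "if any DRP is detected, the PharmDISC tool". For the timing of acceptance, Table 1 says: "Pharmacists will complete the PharmDISC tool during the second and third consultation".

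Two analysis sets are planned. The first is complete cases: "An analysis with completed cases will be made (patients with data for the three consultations". The second is the whole sample, in which the "initial value will be considered as not been modified (baseline observation carried forward-BOCF". Neither sentence says what happens when a patient attends and nothing is proposed.

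**The concern.** A patient with no DRP at a consultation normally has no form, no intervention and hence no denominator, so the specified difference cannot be formed. This is foreseeable. The eligibility criteria do not require a DRP at entry, patients are randomly pre-selected, and the Sample size section expects DRPs to fall, so zeros should become more common at later consultations.

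Whether the difference exists therefore depends on the DRP count at both consultations, which is the quantity the service is meant to change. A result from the remaining patients would describe those who had interventions at both consultations, yet could be read as a result for the whole study. Where the difference does exist, a patient with one intervention, whose proportion can only be 0% or 100%, counts as much as a patient with six.

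**Working it through.** **1. The rule applied to three illustrative patients** (first consultation, then a later one).

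| Patient | First | Later | Difference | Complete cases | BOCF, if 0/0 is coded missing |
|---|---|---|---|---|---|
| A | 1 of 2 | 1 of 1 | 1 − 0.5 = +0.5 | +0.5 | +0.5 |
| B (cleared) | 2 of 2 | none proposed | undefined | not usable | 1 carried forward, change 0 |
| C (none at baseline) | none proposed | 1 of 1 | undefined | not usable | no baseline to carry, undefined |

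B is lost in one analysis and scored as no change in the other. C has no value in either.

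**2. What the sample size implies.** Inputs from the Sample size section: difference 0.5 DRP, one-sided 5%, power 0.80, intra-cluster correlation 0.02, dropout 15%, 162 patients, 5–10 per pharmacy. The SD of the change is not given, so 162 cannot be reproduced independently; it can be solved back with a paired-mean formula.

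- Completers: 162 × 0.85 = 137.7.
- Design effect 1 + (m − 1) × 0.02: 1.08 for m = 5, 1.18 for m = 10.
- Effective n: 137.7/1.08 = 127.5; 137.7/1.18 = 116.7.
- SD = 0.5 × √n / (1.645 + 0.842): about 2.27 (m = 5) and 2.17 (m = 10).

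**3. Baseline means that fit this SD.** The protocol gives no mean, so the following is assumed: counts with mean μ at the first consultation and μ − 0.5 at the third, every DRP leading to an intervention, and none without a DRP.

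- Independent Poisson: variance of change = 2μ − 0.5. SD 2.17 gives μ = (4.71 + 0.5)/2 = 2.60; SD 2.27 gives (5.15 + 0.5)/2 = 2.83.
- Shared gamma frailty with variance 1 (assumed): variance of change = 2μ − 0.5 + 0.25 = 2μ − 0.25. SD 2.17 gives μ = 2.48; SD 2.27 gives 2.70.

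The baseline mean is therefore about 2.5 to 2.8.

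**4. Share of third-minus-first differences that are undefined.**

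- Poisson: 1 − (1 − e^−μ)(1 − e^−(μ−0.5)).
  - μ = 2.60: 1 − 0.926 × 0.878 = 0.19.
  - μ = 2.83: 1 − 0.941 × 0.902 = 0.15.
- Frailty: 1/(1 + μ) + 1/(μ + 0.5) − 1/(2μ + 0.5).
  - μ = 2.48: 0.287 + 0.336 − 0.183 = 0.44.
  - μ = 2.70: 0.270 + 0.312 − 0.169 = 0.41.

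Of 137.7 completers, about 112 to 117 (Poisson) or 77 to 81 (frailty) would have a usable difference.

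**5. Who the undefined patients are.**

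- Frailty: no DRP at the first consultation 27–29% of all patients; cleared (a DRP first, none at the third) 0.312 − 0.169 = 14% to 0.336 − 0.183 = 15%. About two thirds of the undefined group had nothing to clear.
- Poisson: no DRP at the first consultation 6–7%; cleared 9–11%.

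The undefined group is a mixture under either model.

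**6. Recording schedule.** Table 1 has acceptance entered at the second and third consultations only. If an entry refers to proposals made at the preceding consultation, acceptance of third-consultation proposals has no scheduled entry. If it refers to the same consultation, acceptance at the first has none. Either way the third-minus-first contrast lacks one side until this is clarified; under the same-consultation reading the second-minus-first contrast does too. Steps 3 to 5 assume that both sides are available.

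**The case against.** The strongest reply is that the protocol contains no rule dropping anyone, and that a convention for zero denominators is a detail an article may leave to a fuller plan. The first part stands. A reader might infer that the plan excludes patients whose DRPs cleared. No sentence says so: exclusion follows only in the complete-case analysis, the carried-forward analysis could keep those patients with a change of 0, and the undefined group also holds patients with no DRP at baseline. The second part does not dispose of the point, because the article itself fixes the patient as unit, the difference as contrast and the proportion as measure. Any convention for 0/0 would have to assign an acceptance to interventions never proposed, or leave the patient out.

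A reader might also infer that most patients are lost. At a baseline mean of 1 the same models give 75–77% undefined, but their SD of change is only √1.5 = 1.22 to √1.75 = 1.32, which does not fit the 2.17–2.27 implied by the planned sample size.

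Importance can be overstated too. Acceptance is primary only by its place in Table 1. The Abstract names identification of DRPs as the primary outcome and lists interventions as secondary, the Discussion speaks of a single primary measure, and the sample size rests on the DRP count, which is properly defined at zero.

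Finally, an intervention-level analysis does not remove the selection, since cleared patients still contribute nothing at the later consultation. That is correct and limits what the remedy can claim.

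**Conclusion.** The concern holds in limited form. The stated measure has no value for a foreseeable group of attending patients, membership of that group depends on the DRP count, and the two planned analyses treat the group differently, so comparing them would not show the problem for what it is. Under count models consistent with the planned sample size, roughly 15–19% (independent Poisson) to 41–44% (shared gamma frailty) of third-minus-first differences are undefined. These figures rest on an assumed count distribution, an assumed frailty variance of 1, a paired-mean reading of the sample size, and one or more interventions for every DRP; none of these is stated in the protocol. The effect is confined to the acceptance outcome. The analysis of the DRP count and the sample size are not touched. The sentence should be changed before analysis.

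**What to change.** - Remove the acceptance proportion from the list of per-patient differences in Statistical methods and analysis.
- Model accepted yes/no for each proposed intervention, with consultation as a factor, using a logistic mixed model or GEE that accounts for patient within pharmacy.
- At each consultation report pooled accepted/proposed with a cluster-robust 95% confidence interval and, beside it, the number of patients with no intervention.
- State that a consultation with no intervention is not missing data for the carried-forward analysis.
- Reconcile the recording of acceptance at the second and third consultations only with the planned contrasts against the first, saying to which consultation's proposals each entry refers.

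The cost is a few sentences and one standard model. No new data item is needed, as PharmDISC is already the planned record of interventions and their acceptance, provided the recording schedule is settled. There are two downsides. Patients with many interventions weigh more. Later consultations still reflect only patients with remaining or new DRPs, so the change should be described as a change among proposed interventions, not as a change in patients.

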## Materials and methods

### Study design and setting

A pre-post intervention study with a cluster design and one intervention group will be carried out in Swiss CPs in the canton of Vaud. The study is taking place for 15 months between April 2023 and June 2024 and it will follow the standard protocol items SPIRIT [24] (see Fig 1 and S1 Appendix).

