### Study measurements and outcomes

Dependent study outcomes and variables are presented in Table 1. In addition, independent variables will be collected in relation to patients (socio-demographic characteristics variables: gender, year of birth and education level and treatment variables: brand name/DCI, dose, formulation, posology for each medicament); pharmacists (socio-demographic characteristics: gender and year of birth and academic and work-related characteristics: role (manager/not manager), year of graduation in pharmacy, place of graduation in pharmacy, working hours in the CP) and CPs (average prescriptions per day, opening hours, location (urban/suburban/rural/industrial area), number of pharmacy technicians and pharmacists employed).

**Table 1 pone.0292037.t001:** Study outcomes.

Primary outcomes (type of variable)	Definition and assessment	Time point
Number of DRPs detected (quantitative)	DRPs associated with patients’ behavior detected by the pharmacist before the consultation (evaluation of the medication) and during the consultation (evaluation of patients’ information). Total number of DRPs and mean per patient and depending on the number of the patients’ medication will be calculated.	Pharmacists will complete the medication plan and PharmDISC tool before and during the consultation.
Evolution on the number of DRPs (quantitative)	Evolution on the number of DRPs associated with patients’ behavior detected will be assessed by comparing the differences between the three consultations with the patient.	Research team will calculate the differences using the medication plan at each consultation.
DRP classification (qualitative)	PharmDISC tool will be used for DRP related classification (15 DRPs related to patients’ behavior out of the 24 total DRP included in the tool): 1. Drug choice: duplicate, accumulation, adverse event. 2. Dose choice: under dose/overdose. 3. Drug use: a. inappropriate timing or frequency of administration, b. inappropriate use method, c. inappropriate treatment duration. 4. Patient: insufficient adherence, insufficient knowledge, burden due to therapy, inappropriate stockage, absence of label. 5. Logistics: prescribed drug not available, error in medication process. 6. Other (to be detailed by the pharmacist).	Pharmacists will complete the PharmDISC tool before and during the consultation.

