### Sample size

Primary objective of the study aims to measure the difference in DRPs per patient observed between consultations. Sample size calculation was based on this primary study outcome to detect a difference of 0.5 DRP per patient at the end of the study (using a one-tailed test because the hypothesis is that patients will have a decrease of DRPs at the end of the study). The calculation was based on a pilot study carried out on 20 patients at Unisanté CP. Sample size was calculated with ≥0.8 power, type I error rate of 5%, assuming an intra-cluster correlation of 0.02. Allowing for 15% dropout, the overall sample size is 162 patients, with 19 to 35 pharmacies (5–10 patients per CP).

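### The only analysis said to account for clustering is a model built by p-value screening (p<0.2, then p<0.1), and the unscreened mean change that the study is powered for is not named as the primary analysis

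*Protocol article*

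**What the plan says.** The section Study design and setting describes a single-arm study: "A pre-post intervention study with a cluster design and one intervention group will be carried out in Swiss CPs in the canton of Vaud". The section Sample size sets the target: "Primary objective of the study aims to measure the difference in DRPs per patient observed between consultations". The calculation is made "to detect a difference of 0.5 DRP per patient at the end of the study", with an intra-cluster correlation of 0.02.

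The section Statistical methods and analysis first lists general tests for continuous variables (Student's t, ANOVA, Kruskal-Wallis) and does not mention clustering there. It then says that each patient's differences (second minus first, third minus first consultation) will be compared, and that a linear regression will account for the cluster effect. After a sentence on a sub-analysis of patients who pre-select their medication, it gives the model-building rule: "Firstly, variables will be considered significant (p-value<0.2) in a bivariate model to be included in a multivariate model", and then "the variables considered significant at a value of p<0.1 in the multivariate model will be included in the final model". The significance level is p<0.05.

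The section does not name the pool of candidate variables. The natural source is Study measurements and outcomes: "In addition, independent variables will be collected in relation to patients", followed by pharmacist and pharmacy variables.

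**The concern.** There are two separate difficulties.

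**What the model estimates.** The response is a change score and there is no comparison group, so no coefficient represents the service. The quantity the study is powered for is the mean change. A regression constant equals that mean when there are no covariates, or when every covariate is centred. With an uncentred covariate, the constant is the expected change at covariate value zero, which has no useful meaning for a variable such as year of birth. The text mentions neither centring nor a marginal mean, and it does not say which estimate is primary. The cluster effect, which the sample size relies on, is attached only to this regression.

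**What its p-values mean.** The same data choose the covariates and then test them. A covariate is kept because its p-value was small, and that p-value is then judged at 0.05 as if the covariate had been fixed beforehand.

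At stake are a clear, cluster-adjusted answer to the primary question and the credibility of any predictor of change that is reported.

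**Working it through.** **1. The plan's own figure.** The inputs in the section Sample size are a difference of 0.5, one-tailed 5%, power 0.80, intra-cluster correlation 0.02, 15% dropout and 5–10 patients per pharmacy. For a mean change, N = [(1.645 + 0.842) × SD / 0.5]² × [1 + (m − 1) × 0.02] / 0.85. The standard deviation of the change is not given, so 162 cannot be reproduced directly. Solving backwards with 162 × 0.85 = 137.7 completers:
- m = 5, design effect 1.08: SD = 0.5 × √(137.7/1.08) / 2.486 = 2.27
- m = 10, design effect 1.18: SD = 0.5 × √(137.7/1.18) / 2.486 = 2.17

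The stated 162 therefore fits a cluster-adjusted test of the mean change with an SD of about 2.2. This is an unscreened quantity with no covariates.

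**2. Candidates.** Counting the listed variables: patients 3 (gender, year of birth, education); pharmacists 6 (gender, year of birth, role, year of graduation, place of graduation, working hours); pharmacies 5 (prescriptions per day, opening hours, location, number of technicians, number of pharmacists). The total is 14, not counting treatment variables. That all 14 enter the screen is an assumption.

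**3. p-values after the screen.** A noise covariate with a well-behaved p-value that has passed p<0.1 is below 0.05 about 0.05/0.10 = 50% of the time, before any few-cluster effect. The stated rule was simulated with no real predictor, using cluster-robust standard errors:
- 14 candidates, 138 completers: a noise covariate in the final model had p<0.05 in about 56–72% of cases.
- 8 or 15 candidates, 28 × 5 or 19 × 7 completers, SD 2.2: 61–73%.

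**4. Does the screen raise the overall chance of a false predictor?** Proportion of simulated trials with at least one noise covariate at p<0.05 (14 candidates, 138 completers):

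| Setting | With the screen | Separate tests, no screen |
|---|---|---|
| 19 pharmacies | 67% | 69% |
| 35 pharmacies | 65% | 64% |
| all covariates at patient level | 52% | 52% |

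Fourteen independent 5% tests would give 1 − 0.95¹⁴ = 51%. The screen adds essentially nothing. The base is multiplicity, and the excess in the first two rows comes from cluster-robust standard errors for pharmacy-level covariates with few clusters.

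**5. What happens to the mean change.** Coverage of the true mean change by a nominal 95% interval:
- Model with no covariates: 94–95% (standard error about 2.2 × √(1.08/140) = 0.19)
- Average predicted change, that is, the constant after centring, from the screened model: about 91–95%
- Uncentred constant of the screened model, when covariates are kept: 49–53%, with the covariate scales assumed in the simulation

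The third line matters only if the uncentred constant were reported as the effect. The text neither says this nor excludes it.

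**The case against.** The best defence is that the screened regression is not the primary analysis. The section says that the differences will be compared and names simple tests, and Table 1 defines the evolution of drug-related problems as differences between the three consultations. The screening sentences follow the pre-selection sub-analysis, so they can be read as a secondary predictor model. On that reading the mean change is obtained elsewhere. This stands in part: a test of mean change is not absent. But the simple tests are listed without the cluster effect, the text does not call the regression exploratory, and it calls its end product the final model. The thresholds are also stated rules, not details left to an analysis plan.

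Three stronger readings are tempting, and the documents do not support them.
- A reader might infer that the screen itself drives a high overall rate of false predictors. Unscreened tests of the same candidates give the same rate.
- A reader might infer that the standard error of the effect would explode because year of birth enters uncentred. That needs year of birth to be selected, left uncentred and the constant reported as the effect; no section states this, and a centred mean is only mildly affected.
- A reader might infer that screened predictors will be used to target the service. The only targeting remark concerns the sub-analysis of patients aged 65 or over, a group named in advance.

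**Conclusion.** The point holds in a limited form. The plan fixes a two-step p-value screen for the only analysis that it says accounts for clustering, and it does not name the unscreened, cluster-adjusted mean change as primary, although the sample size is built on that quantity. Retained covariates cannot be judged at 0.05 at face value: about 56–72% of noise covariates that reach the final model would pass. A mean taken from the screened model after centring would be only slightly too optimistic (coverage about 91–95%), so this is a flaw of specification and interpretation that does not invalidate the study.

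The figures rest on assumptions: an SD of change near 2.2 (back-solved), covariate scales, 8 to 15 candidates, 19 to 35 pharmacies and no real predictor. The sizes vary with these. The low value of p-values after selection follows from the rule itself.

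**What to change.** In the section Statistical methods and analysis:
- State that the primary analysis is the mean change in the number of drug-related problems per patient from first to third consultation, with a 95% confidence interval, from a model that accounts for pharmacy and contains no selected covariates.
- If an adjusted estimate is wanted, fix a short covariate list in advance (for example age, number of chronic drugs, pre-selection of medication) and centre the covariates, so that the constant remains the mean change.
- Delete the p<0.2 and p<0.1 screens.
- Label the predictor model exploratory, and report every candidate with its confidence interval and without significance claims. This does not lower the chance that some interval excludes zero; it removes the selection and shows how many candidates were examined.

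The cost is analysis wording only. No data item or sample-size input changes, so the target stays at 162 patients.
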